### Participant timeline {13}

The schedule of study outcomes is assigned in Table 1.

**Table 1 Tab1:**
[figure not shown]
The enrolment, intervention, assessment, and visit schedule for the participants

The X indicates at which point of the trial the respective assessments will take place

### Sample size {14}

Using the G*Power software (Germany) [46], a sample size of 48 (*n* = 24 per group, 1:1 allocation) is calculated based on the highest attrition rate of 40% at 3rd month follow-up of the study to retain a sample size of *n* = 28, according to similar research [47]. The calculation is according to the *F* test-repeated measures ANOVA, between factors, with an effect size of 0.3, an alpha level of 0.05, (1 − *β* err prob) = 0.8 to detect a significant change of the area of COP from 42.0 (± 23.6) to 25.4 (± 8.2) [48].

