### Statistical methods

#### Statistical methods for primary and secondary outcomes {20a}

SPSS version 26.0 will be used to analyze the primary and secondary outcomes based on the intention to treat (ITT) principle. ITT analysis will be performed using all randomized patients, including data for those terminated or lost to follow-up. During the process, assumptions will be checked, and remedial measures will be employed. The normality of the data will first be determined using the Kolmogorov–Smirnov test or the Shapiro–Wilk test (*p* > 0.05) to test for the normality of the data distribution. Other graphical methods such as Q-Q plots or histograms will also be used for visual inspection of the distribution and to assess the normality. If skewness and heteroscedasticity are present, transformation methodology such as Logarithm may be applied to make the distribution more symmetric and stabilize the variance. Baseline data and clinical variables between both groups will be compared using independent Student’s* t*-tests (parametric)/Mann–Whitney *U* test (non-parametric) for continuous data and the χ^2^ of independence for categorical data, respectively. Descriptive statistics will be presented in either mean (SD) or frequency (%). Thereafter, a repeated measure analysis of variance (RMANOVA) will be used to measure the time/exposure effects of muscle strength, Y balance test, LSDT, SLT, DROM, and results of the questionnaire between baseline, week 4, week 8, 3rd month, 6th month, and 1-year follow-up. Analysis of covariance (ANCOVA) will be conducted for baseline characteristics and prognostic factors as covariates and compared for group differences in different time points. Repeated-measure ANOVA and ANCOVA will be applied for all participants who have completed the assessments post-treatment. Bonferroni correction will be performed for multiple comparisons. Sensitivity analysis will be conducted by comparing the results of the imputation method to complete-case and available data analyses. The significant level will be set at 0.05.

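### The 40% attrition allowance is justified only to month 3, but the repeated-measures ANOVA runs to 1 year under conflicting analysis-set rules, so the stated 80% power is not established for it

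*Protocol article*

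**What the plan says.** Sample size {14} gives "24 per group, 1:1 allocation", so 48 in total, and explains this by "the highest attrition rate of 40% at 3rd month follow-up", chosen "to retain a sample size of *n* = 28". The powered test is the G*Power F test for "test-repeated measures ANOVA, between factors", with "an effect size of 0.3, an alpha level of 0.05" and power 0.8. Neither the number of measurements nor their correlation is given.

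Statistical methods {20a} runs the repeated-measures ANOVA "between baseline, week 4, week 8, 3rd month, 6th month, and 1-year follow-up", which is six visits. On who enters it, the section says: "Repeated-measure ANOVA and ANCOVA will be applied for all participants who have completed the assessments post-treatment".

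The same section also promises an intention-to-treat analysis of everyone randomised, including those lost to follow-up, and uses complete-case results as a comparator for the imputed ones. The section on non-adherence and missing data {20c} repeats intention to treat and plans multiple imputation, with data assumed missing at random.

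**The concern.** Three items that should fit together do not: the date attached to the attrition allowance, the span of the powered analysis, and the set of participants who enter it. The allowance is dated to month 3. The analysis ends nine months later, and no attrition figure is given for month 6 or month 12. A standard repeated-measures ANOVA without imputation drops anyone who misses a listed visit, so in a completer set the number at 1 year can equal the month-3 number but cannot exceed it.

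What is at stake is how a null long-term result is read. A reader would set it against 80% power, although the protocol supports that figure at most up to month 3, and only under inputs it does not state. The conflict over the analysis set also leaves open whether the number analysed is 48 or the number of completers.

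**Working it through.** **Inputs from the protocol.** Total 48, 24 per group; attrition 40% at month 3; 28 retained; effect size f = 0.3; alpha 0.05; power 0.80; between-factors repeated-measures ANOVA (Sample size {14}). Six visits to 1 year (Statistical methods {20a}).

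**Inputs assumed here, because the protocol does not give them.** Attrition at 12 months; number of measurements m in the power calculation (6, matching the planned ANOVA); correlation ρ between repeated measures.

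**Step 1: the plan's attrition figure.** 28 / (1 − 0.40) = 46.7, so 47, or 48 in equal arms. In the other direction, 48 × 0.6 = 28.8. This step reproduces; the reserve is 0.8 of a participant.

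**Step 2: the threshold.** 48 − 28 = 20 losses, and 20/48 = 41.7%. A 21st loss (21/48 = 43.8%) leaves 27.

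**Step 3: power below 28, taking 80% at 28 as given.** Noncentral F with 1 and N − 2 degrees of freedom, alpha 0.05. The noncentrality that gives 80% at N = 28 is λ = 8.47; for other N it is scaled by N/28.

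| Assumed loss by 12 months | Complete at every visit | λ | Power |
|---|---|---|---|
| 40% | 28 | 8.47 | 80% |
| 21 of 48 (43.8%) | 27 | 8.17 | 78% |
| 45% | 26 | 7.87 | 77% |
| 50% | 24 | 7.26 | 73% |
| 60% | 18 (19.2, rounded down to equal arms) | 5.45 | 59% |

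**Step 4: does 28 give 80%?** For the named between-factors test, λ = f² × N × m / (1 + (m − 1)ρ). With f = 0.3, N = 28 and m = 6, the numerator is 0.09 × 28 × 6 = 15.12.

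- Reaching λ = 8.47 needs 1 + 5ρ = 15.12/8.47 = 1.785, so ρ is about 0.16.
- At ρ = 0.5, λ = 15.12/3.5 = 4.32 and power is 52%.
- At ρ = 0.5 with all 48 analysed, λ = 25.92/3.5 = 7.41 and power is 76%; 54 analysed are needed for 80%.
- With m = 3 and ρ = 0, λ = 0.09 × 28 × 3 = 7.56 and power is 75%. With m = 2 and ρ = 0, λ = 5.04 and power is 58%. For this test a positive correlation only lowers these figures.

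So 28 matches the named test only for a low correlation combined with four or more measurements (for m = 4 the largest ρ that works is 0.063, for m = 5 it is 0.121).

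**The case against.** The strongest reply is that a shortfall is not shown. A reader might infer that the 1-year analysis will be run on fewer than 28 participants, so that the 80% is simply false. The protocol does not support that, for three reasons.

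- No 12-month attrition is stated, and 40% is called the highest rate. If it is a ceiling for the whole follow-up, 28 remain.
- Treatment lasts 8 weeks, so completing the post-treatment assessments could mean the week-8 visit rather than every visit to 1 year.
- Intention to treat and multiple imputation are both planned. If they govern, all 48 are analysed and nobody is dropped for a missed visit, although imputation does not restore all the lost information.

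It can also be said that power-software settings are detail a condensed article may leave to the full protocol, and that a mixed model and multiple imputation handle data missing at random in much the same way.

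These points make the loss of power conditional, and that much stands. They do not supply a justification for months 6 and 12, since the text ties the 40% to month 3. Nor do they remove the conflict between the completer sentence and the intention-to-treat statements: if imputation governs, a calculation on 28 retained participants does not describe the planned analysis; if the completer sentence governs, the allowance stops short of it. The missing settings are not the fault in themselves. The point is that the stated effect size, test and number retained give 80% only in a narrow range of those settings.

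**Conclusion.** The point holds in conditional form. The attrition arithmetic is correct, but the allowance is justified only to month 3 and has almost no reserve, while the powered analysis runs to 1 year and its analysis set is stated in two incompatible ways. If the 1-year ANOVA is run on participants complete at every visit, losing more than 20 of 48 takes the set below 28. The cost in power is small at first (77% at an assumed 45% loss, 73% at 50%) and larger beyond that.

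Separately, the 80% at 28 requires a correlation of about 0.16 or less with six measurements, and falls to 52% at an assumed 0.5. The 12-month loss rates, m = 6 and ρ = 0.5 are assumptions. The threshold of 20 losses follows from the protocol's own numbers.

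**What to change.** 1. In Statistical methods {20a}, delete the restriction to participants who completed the post-treatment assessments. Make the primary analysis a mixed model for repeated measures on all randomised participants, using every available visit, with multiple imputation and complete-case analysis as sensitivity analyses. A participant lost after month 3 then still contributes the earlier visits, and the primary analysis agrees with the intention-to-treat statement.
2. In Sample size {14}, claim 80% only for a named comparison at or before month 3, under a stated number of measurements and a stated correlation that reproduce the figure. Give power at months 6 and 12 as a range over stated attrition.

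This is a change of wording in the protocol and analysis plan. It asks for no extra enrolment. The downside is that the stated power for long-term follow-up becomes less favourable.

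### The sample-size figures do not fit together: f = 0.3 does not follow from the quoted COP areas, and 28 completers give 80% power only at a low, unstated correlation

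*Protocol article*

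**What the plan says.** Sample size {14} names G*Power and describes the test as "repeated measures ANOVA, between factors, with an effect size of 0.3, an alpha level of 0.05", with power 0.8. It randomises 48 participants, 24 per group, and explains that number as "based on the highest attrition rate of 40% at 3rd month follow-up of the study to retain a sample size of" 28. The calculation is said to be able "to detect a significant change of the area of COP from 42.0" (SD 23.6) to 25.4 (SD 8.2), citing an earlier study.

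The section does not give the number of measurements or the correlation entered, does not show how f was obtained, and does not say whether the two COP means are two groups or two time points.

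Three other sections bear on the point. Outcomes {12} schedules six assessments: baseline, weeks 4 and 8, and months 3, 6 and 12. Intervention description {11a} gives both arms the same exercise programme. Statistical methods {20a} promises an intention-to-treat analysis of everyone randomised, but also applies repeated-measures ANOVA and ANCOVA to those who completed the post-treatment assessments.

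**The concern.** The paragraph offers one chain: a COP-area effect, an effect size f, a test, a power, a completer number and a randomised number. Two links can be checked, and neither holds as written.

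First, f should follow from the means and SDs that the section quotes, and it does not. Second, the power of a between-factors repeated-measures test depends strongly on the correlation among a participant's measurements, because the test compares participant averages: the higher the correlation, the less each extra visit adds. A completer number of 28 at f = 0.3 implies a low correlation that nobody has stated or defended.

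The stake is how the result will be read. A null finding would be reported as coming from a trial with 80% power for its planning effect. At correlations of 0.5 or more, the chance of detecting f = 0.3 with 28 completers is about one half or less. Nor can a reader tell which effect the trial was planned to detect.

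**Working it through.** **Inputs from Sample size {14}:** two groups, f = 0.3, alpha 0.05, power 0.8, 40% attrition, 28 retained, 48 randomised, COP area 42.0 (SD 23.6) and 25.4 (SD 8.2). **From Outcomes {12}:** six scheduled assessments. **Assumed, because not stated:** the number of measurements m and the correlation rho used in the calculation. Both are varied below.

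**Attrition step.** 28 / (1 − 0.40) = 46.7, so 47, or 48 for equal groups. In reverse, 48 × 0.6 = 28.8. This step reproduces.

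**Effect size.** For two equal groups, f = d/2 with d = difference / SD.

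- Difference: 42.0 − 25.4 = 16.6.
- Pooled SD: √[(23.6² + 8.2²)/2] = 17.67. Then d = 16.6/17.67 = 0.94 and f = 0.47.
- Larger SD alone: d = 16.6/23.6 = 0.70 and f = 0.35.
- f = 0.3 means d = 0.6, which needs an SD of 16.6/0.6 = 27.7. That exceeds both quoted SDs, so no average of the two can produce it.
- With the pooled SD, f = 0.3 is a difference of 0.6 × 17.67 = 10.6, not 16.6.

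**Power of the stated test.** The noncentrality is lambda = N f² m / [1 + (m − 1) rho], referred to a noncentral F with 1 and N − 2 degrees of freedom.

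Example: N = 28, f = 0.3, m = 6, rho = 0.5 gives 28 × 0.09 × 6 / 3.5 = 15.12/3.5 = 4.32 and power 0.517.

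Power at f = 0.3 with six measurements:

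| rho (assumed) | N = 28 | N = 48 |
|---|---|---|
| 0.3 | 66% | 88% |
| 0.5 | 52% | 76% |
| 0.7 | 42% | 65% |

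**What would make 28 correct.** With m = 6 and rho = 0.15, lambda = 15.12/1.75 = 8.64 and power is 80.8%, so the stated number can be reached. The largest rho that still gives 80% at N = 28 is:

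- 0.157 with six measurements
- 0.122 with five
- 0.063 with four, which is the number of assessments up to month 3, the visit to which the 40% attrition is tied
- none with three or two: even at rho = 0, power is 75% and 58%.

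At rho = 0.5, N = 28 gives 42% (m = 2) to 52% (m = 6), and 80% at m = 6 would need 54 completers. The smallest f with 80% power at N = 28, m = 6 and rho = 0.5 is about 0.42.

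**If the COP figures, not f = 0.3, are the planning effect.** At rho = 0.5 and N = 28, f = 0.47 gives 79% (m = 2) to 88% (m = 6), and f = 0.35 gives 54% to 65%.

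**The case against.** The strongest reply is that a reader might infer from these figures that 28 participants simply do not give 80% power. The document does not support that. Power depends on m and rho, the article states neither, and 28 does reach 80% with six visits and a correlation of about 0.15. The 52% figure belongs to an assumed correlation of 0.5. Leaving G*Power settings out of a journal article is also ordinary condensation. All of this stands, so the power claim is stated here only as a condition on rho. The condition is still worth raising, because the article itself fixes the test, f, alpha, power and N, and together with the six-visit schedule these imply a correlation of about 0.16 or less. That is low for the same person repeating the same single-leg test.

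Second, the effect-size mismatch runs in the safe direction: planning on 0.3 asks for more participants than planning on 0.35 or 0.47, and at f = 0.47 the 80% claim roughly holds. This also stands, so the mismatch is not in itself a source of lost power. It does leave two incompatible effects described as one.

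Third, 28 is a worst case. Intention to treat with multiple imputation is planned (Statistical methods {20a} and the missing-data section {20c}), and if all 48 are analysed with six visits, power stays at 80% or more up to a correlation of about 0.43. This holds in part, since {20a} also restricts the repeated-measures ANOVA and ANCOVA to participants who completed the post-treatment assessments.

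Last, the wording of a change from one value to another tempts one to say that a pre-post change was used to size a between-group test. The article does not say whether the two means are groups or time points, so that is not established. What can be said is that the wording leaves it open. The distinction matters because both arms receive the same exercise programme, so a change over time in one arm would not be the active-versus-sham difference.

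**Conclusion.** The point holds in conditional form. On the document's own numbers, f = 0.3 does not correspond to 42.0 (SD 23.6) versus 25.4 (SD 8.2) read as the two-group contrast that a between-factors test requires. The only assumption in that conclusion is the two-group reading.

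The stated 80% power at 28 completers is neither confirmed nor refuted by the document, because it rests on a low correlation that is not stated. If the true correlation is 0.3 to 0.7, power at f = 0.3 with six visits is about 66% down to 42%, and the month-3 framing of the completer number makes the condition stricter. These figures assume equal correlations between visits and complete data on those counted.

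**What to change.** Revise Sample size {14} without changing enrolment:

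- State the number of measurements, the correlation and the between-group COP-area difference actually used, and say whether the cited means are groups or time points.
- Derive f from that difference and its SD. Remove the link between f = 0.3 and 42.0 versus 25.4 unless the derivation can be shown.
- Restate power at 28 and at 48 over a plausible range of correlations, or give the detectable effect (for example, f about 0.42 at N = 28 with six measurements and an assumed correlation of 0.5). No single correlation should be presented as fact without a source. Alternatively, re-derive power for the baseline-adjusted ANCOVA already named in Statistical methods {20a}.

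The cost is rewording and one rerun of the calculation, with no extra participants. The drawback is that the stated power may become less favourable.

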### Recruitment {15}

Participants will be principally recruited from the Department of Orthopaedics and Traumatology, Prince of Wales Specialist Outpatient Clinic. The orthopedic surgeons will screen the participants based on their clinical symptoms and explain the details of the study to the participants. Furthermore, the recruitment information for the trial will be delivered to various sports teams and through the internal mass-mail system at CUHK. They will be referred to the research team for eligibility assessment at the Sports Injury and Biomechanics Laboratory should they want to join the trial.

### Assignment of interventions: allocation

#### Sequence generation {16a}

Participants will be randomly assigned to a unique radiofrequency identification (RFID) card number in a 1:1 ratio by an online research randomizer (https://www.randomizer.org/). The unique RFID card is provided by the Quantum TX. Each allocation will be tagged with a unique RFID card generated by the chief engineer from Quantum TX and is recognized by the PEMF machine.

#### Concealment mechanism {16b}

The randomization will be conducted using an online research randomizer by the chief engineer at Quantum TX and the random order of the treatment allocation will only be shared with the biostatistician, a third party based at the CUHK who is not involved in the recruitment process. The randomization will not be disclosed to either the participants or the trial assessors throughout the intervention period. The participants will be randomly assigned to a unique and identical RFID card in which the PEMF or the sham group are randomly allocated to the RFID card. This is to ensure that the participants and the assessors are both blinded to the unique RFID cards containing the treatment types.

#### Implementation {16c}

The chief engineer of Quantum TX will generate the randomization, and the randomization results will only be shared with the biostatistician at the CUHK. The research team and the orthopedic surgeons will recruit the participants. The Ph.D. student will assist in the assessment and assign the participants to the interventions. At the end of the intervention, the biostatistician will reveal the randomization results to the research team and orthopedic surgeons for statistical analysis.

### Assignment of interventions: blinding

#### Who will be blinded {17a}

The assessors and orthopedic surgeons will be blinded to the assignment of the interventions. Since the PEMF therapy will not elicit heat or sensation, the participants will also be blinded to the treatment allocation. The randomization results will only be disclosed to the assessors and the orthopedic surgeons after the PEMF intervention has ended.

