### Trial design {8}

This is a prospective randomized, double-blind, placebo-controlled trial with two parallel groups and a 1:1 allocation ratio to investigate the treatment effects of PEMF for participants with CAI. All participants will be randomized into an intervention group (*n* = 24, active PEMF and SC) and the control group (*n* = 24, sham PEMF and SC). Researchers will perform all patient-reported outcome measures (PROM), functional, and ultrasonographic outcomes during baseline assessment, 4 weeks, 8 weeks, and follow-up visits on the 3rd month, 6th month, and 1 year after the commencement of the trial. An overview of the study is displayed in Fig. 1.

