### Intervention description {11a}

Participants randomized into the experimental group will be exposed to PEMF therapy employing a BIXEPS device (Quantum TX Pte. Ltd., Singapore) as previously described by Venugobal et al. [19]. Exposure will be given twice a week for 8 weeks for a total of 16 sessions on their affected foot in adjunct with SC. Each treatment session will last for 10 min. The active PEMF therapy does not produce any sensation, facilitating the blinding process. Meanwhile, the control group will receive the SC and the sham treatment from the same PEMF device. A team researcher will operate the PEMF device and monitor any clinical changes during the randomized clinical trial. Each participant will be tagged with a unique radiofrequency identification (RFID) card supplied by Quantum TX Pte. Ltd. using block randomization to assign the treatment group. To mitigate any selection bias, the block size will be concealed from the investigators, and all will be blinded from the subjective assignment.

A team researcher will be responsible for turning on the PEMF machine for all the participants using the RFID cards. A biostatistician not involved in the participant recruitment will oversee the randomization procedure. Both the research team and the biostatistician will remain blinded during the trial. Participants will use the RFID card to complete the treatment without knowledge of group allocation. Side effects will be reported if there are any.

The treatment procedure requires that the participant be seated at 90 degrees on a chair. The solenoids will be adjusted to cover the lower limb. The BIXEPS device is set to low frequency and amplitude fields (1 mT and 50 Hz) to be applied to the affected limb for 10 min. Sham PEMF therapy and SC will be used for the control group. Since the PEMF therapy does not elicit any sensation, both groups are blinded, and the same SC regime will be administered to both groups. Figure 2 depicts how the participants will be situated relative to the BIXEPS device.

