##### The elasticity of the peroneal muscle

In addition, the shear elastic modulus of a muscle will be measured using ultrasonic shear wave elastography (Aixplorer, Supersonic Imagine, France) with a linear array probe. The region of interest (ROI) will be set near the center of each muscle. The analysis area will be a 5-mm diameter circle at the center of ROI. The shear elastic modulus will be measured three times per muscle, and the average of the three measured values will be used for further analysis. The shear elastic moduli of the PL and PB will be measured at proximal 25% from the head of the fibula to the lateral malleolus. For each Q-box, the maximum, minimum, and mean (in kPa) of the stiffness of the muscle are measured [41].

Other patient-reported outcome measures (PROM) will be employed to assess overall health and foot and ankle-related symptoms, pain, physical activity level, and health-related quality of life. Foot and Ankle Ability Measure (FAAM) will be used to assess the foot and ankle functional limitations among CAI individuals. The FAAM consists of 29 items, scored between 0 and 4, divided into two subscales: activities of daily living (21 items) and sports (8 items) [42]. For score analysis, the percentage of each subscale is used separately. According to the International Ankle Consortium, values of the day living activities < 90% and < 80% of the sports subscales of the FAAM score were considered unsatisfactory. Manchester-Oxford foot and ankle questionnaire (MOXFQ) is a 16-question self-reported score designed to evaluate the impact of foot and ankle problems on a person’s quality of life. The dimensions comprise 3 subscales: walking/standing problem (7 items), foot pain (5 items), and issues related to social interaction (4 items). After that, all three domains of the MOXFQ can be summed up and converted to a metric from 0 to 100 to create a summary index score (MOFXQ index) [43]. The pain score will be evaluated using the visual analog scale (VAS) ranging from 0 to 100. For the pain score, the higher the score indicates, the more severe the pain. The Short Form-36 questionnaires (SF-36) will be used to evaluate the health-related quality of life [44]. The International Physical Activity Questionnaire will be used to evaluate the physical activity levels [45]. All primary and secondary outcomes will be evaluated at baseline, 4th week, 8th week, 3rd month, 6th month, and 12th month follow-up.

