#### Data management {19}

The collected data will be entered into Excel and SPSS files. They will all be password-protected and destroyed 5 years after publication in Ph.D. thesis and peer-reviewed journals. The Ph.D. student will be responsible for the data collection, data entry, and data analysis under the guidance of the biostatistician. Double data entry and range checks for data values will promote data quality.

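### Blinding is protected only until the 8-week PEMF course ends, so assessor blinding is not secured for the month-3, -6 and -12 outcomes, and other sections contradict this release time

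*Protocol article*

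**What the plan says.** Trial design {8} gives the label: "This is a prospective randomized, double-blind, placebo-controlled trial with two parallel groups and a 1:1 allocation ratio". Intervention description {11a} fixes the length of treatment: "Exposure will be given twice a week for 8 weeks for a total of 16 sessions".

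Three sections tie the release of allocation to the end of that treatment:

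- Concealment mechanism {16b}: "The randomization will not be disclosed to either the participants or the trial assessors throughout the intervention period".
- Implementation {16c}: "At the end of the intervention, the biostatistician will reveal the randomization results to the research team and orthopedic surgeons for statistical analysis".
- Who will be blinded {17a}: "The randomization results will only be disclosed to the assessors and the orthopedic surgeons after the PEMF intervention has ended".

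Measurement continues well beyond that point. The last paragraph of the outcomes section says: "All primary and secondary outcomes will be evaluated at baseline, 4th week, 8th week, 3rd month, 6th month, and 12th month follow-up". Trial design {8} counts the late visits from the start: "follow-up visits on the 3rd month, 6th month, and 1 year after the commencement of the trial". Statistical methods {20a} runs the repeated-measures analysis over all six time points.

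Two sections say something different about blinding. Intervention description {11a} has the research team and the biostatistician blinded for the duration of the trial. Procedure for unblinding {17b} allows unblinding only when an adverse event occurs.

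**The concern.** The double-blind label leads a reader to expect that whoever measures the outcomes does not know the arm at any visit used to compare the arms. The stated rule secures this only during PEMF delivery. After that, the assessors, the orthopedic surgeons and the research team may know the allocation while half of the six scheduled assessments are still to come.

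The stake is detection bias at the late visits. Several secondary outcomes depend on what the assessor does or decides:

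- Eversion strength is measured against the examiner's own resistance.
- Shear wave elastography needs a region of interest to be placed.
- The Y balance and lateral step-down tests have rules on which attempts count.

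Roles also overlap. Implementation {16c} has the Ph.D. student assisting with assessment, and Data management {19} adds: "The Ph.D. student will be responsible for the data collection, data entry, and data analysis under the guidance of the biostatistician". The background gives the long-term effect of PEMF as part of the trial's purpose, so these visits are not incidental.

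**Working it through.** No sample size or power figure is involved, so there is no stated figure to reproduce. The check compares the release time with the visit schedule.

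**Inputs.** Intervention length is 8 weeks = 56 days ({11a}). Post-baseline assessments are at weeks 4 and 8 and months 3, 6 and 12, which makes 5. Planned sample is 48. Enrolment runs from 1 June 2022 to the end of December 2024 (Trial status), which is 944 days. A month is taken as 30.4375 days.

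**Do the late visits fall after week 8?** Weeks after the end of treatment = months × 30.4375 / 7 − 8.

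- Month 3: 13.0 − 8 = 5.0 weeks
- Month 6: 26.1 − 8 = 18.1 weeks
- Month 12: 52.2 − 8 = 44.2 weeks

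All three do.

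**Reading A: the intervention ends at each participant's own week 8.** Every month-3, -6 and -12 visit follows disclosure, so 3 / 5 = 60% of post-baseline assessments do, or 144 of 48 × 5 = 240.

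**Reading B: the intervention ends when the last participant reaches week 8.** Release is then about 31 December 2024 + 56 days = 25 February 2025. Assuming uniform accrual, the share of visits after release = (visit day − 56) / 944.

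| Visit | Calculation | Share | Of 48 |
|---|---|---|---|
| Month 3 | (91.3 − 56) / 944 | 3.7% | 1.8 |
| Month 6 | (182.6 − 56) / 944 | 13.4% | 6.4 |
| Month 12 | (365.25 − 56) / 944 | 32.8% | 15.7 |

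The total is about 24 visits: 24 / 144 = 17% of the late visits and 24 / 240 = 10% of all post-baseline visits, before attrition.

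Weeks 4 and 8 are collected blinded on both readings, provided the week-8 assessment is done before release.

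**Consistency of the sections.**

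| Question | One statement | The other |
|---|---|---|
| Research team | Blinded during the trial ({11a}) | Told at the end of the intervention ({16c}) |
| Biostatistician | Blinded during the trial ({11a}) | Holds the allocation from the start ({16b}, {16c}) |
| Grounds for unblinding | Adverse event only ({17b}) | Routine release at the end of the intervention ({16c}, {17a}) |

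These pairs cannot both hold. No section extends assessor blinding to month 12 in terms specific enough to override {16b}, {16c} and {17a}.

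**The case against.** The strongest reply is that {16c} describes a single hand-over of the randomization results for analysis. That fits one trial-level event at least as well as 48 separate disclosures, and {11a} and {17b} also speak against routine unblinding at each participant's week 8. This stands as far as it goes. A reader might infer that every late outcome is planned to be collected unblinded, but the text does not settle this, and 60% is the upper end of a range. The gap does not vanish on the trial-level reading, where about a third of month-12 visits still follow release.

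Four other inferences go further than the documents:

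- **The primary outcome is equally exposed.** It is centre-of-pressure sway recorded by a pressure mat and processed by software, and the article gives no assessor ruling on which of its trials count. The same assessor supervises the test, so some influence through coaching remains possible, but the risk is lower than for dynamometry or ultrasound.
- **Participants will be told their arm.** They are never named as recipients. Their protection in {16b} does lapse with the intervention period, so blinding of late self-reported outcomes (pain, CAIT, FAAM, SF-36) is not secured. That is weaker than planned disclosure.
- **Performance bias follows.** PEMF and the exercise regimen are described only to week 8, so no trial treatment remains to be delivered differently. Detection bias is the supportable concern.
- **The analyst will choose transformations and covariates knowing the arms.** Release for analysis is stated, but such choices are commonly fixed in a statistical analysis plan, which is not shown.

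**Conclusion.** The point holds. As written, the protocol ends guaranteed blinding of assessors when PEMF ends, although all outcomes are still collected at months 3, 6 and 12 and those visits enter the repeated-measures analysis. This rule also contradicts {11a} and {17b}, so an amendment is needed on any reading.

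Between about 10% and 60% of post-baseline assessments follow disclosure. The upper figure assumes release at each participant's week 8. The lower assumes release at the last participant's week 8, uniform accrual over the stated enrolment dates, and no attrition. The likely harm is detection bias in late assessor-dependent secondary outcomes, with a smaller risk for the primary outcome. The direction and size of any bias cannot be calculated from the document. Blinded collection at weeks 4 and 8 is not in question.

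**What to change.** 1. Amend {16b}, {16c} and {17a} so that allocation is released to assessors, orthopedic surgeons, the research team and participants only after the last participant's 12-month visit and database lock.
2. Run any earlier analysis on coded arms (A/B), and give no arm-level result to anyone who assesses participants.
3. Reconcile {11a} and {17b} with this rule. State whether the biostatistician is blinded, given that {16b} and {16c} give that person the allocation, and how the adverse-event provision relates to the general release time.

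This is a change of wording, with no extra visits or participants. The cost is that an unblinded week-8 report must wait until 12-month follow-up is complete. It should be made before any release takes place, because blinding cannot be restored afterwards.
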